For these reasons it is difficult for anaesthetists to sedate each individual to their preferred level using ACPS. Under-sedation results in an anxious patient because their anxiolytic requirements are unmet during surgery. Over-sedation results in a patient receiving an unnecessarily deep level of sedation and heightened exposure to the associated physiological harms even though the patient would have willingly experienced surgery at a lighter plane of sedation.

Patient-maintained propofol sedation (PMPS) involves the use of a TCI system delivering propofol where the effect-site concentration is influenced by the patient using a handheld trigger. Allowing patients to influence the depth of their sedation with a propofol TCI system has already been described in small case series in healthy volunteers [7] and in general [8], dental [9] and ambulatory outpatient surgery [10]. There are only three randomised controlled trials of PMPS and none of these use the Schnider effect-site-targeted propofol TCI model [5] to compare PMPS against ACPS [11–13]. Our aim is to assess the clinical efficacy of PMPS compared to ACPS. There is no commercially available device to perform PMPS, previous studies having relied on prototype devices. We have therefore designed and built a device capable of delivering PMPS for use in this clinical trial.

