The secondary research objectives are:To establish whether patients are less deeply sedated intra-operatively during patient-maintained sedation compared to anaesthetist-controlled sedation.To assess whether patients undergoing PMPS have equal reductions in peri-operative anxiety compared to patients undergoing ACPS.To observe whether patients undergoing PMPS have comparable post-operative satisfaction with their sedation experience compared to patients undergoing ACPS.To explore whether patients who have undergone PMPS are fit for discharge from the post-anaesthetic care unit (PACU) sooner than patients who have undergone ACPS.To determine if patients undergoing PMPS have calculated effect-site concentrations of propofol that are lower than in patients who undergo ACPS.To examine how many times patients using PMPS press their trigger button to increment their dose (successful button press), how many times they press the button while the device is locked out (unsuccessful button press) and whether there is a relationship between pre-operative anxiety state and use of the trigger system.To determine whether patients undergoing PMPS experience a different incidence of airway, respiratory or cardiovascular sedation-related side-effects than patients who have undergone ACPS. Airway sedation-related side-effects include partial or complete airway obstruction that requires the usual clinical anaesthetist to apply one of the following interventions: chin-lift, jaw thrust, nasopharyngeal airway insertion, oropharyngeal airway insertion, laryngeal mask insertion or endotracheal tube insertion. Respiratory sedation-related side-effects are respiratory rate fewer than 8 breaths per minute or arterial oxygen saturations less than 88% in patients with chronic obstructive pulmonary disease (COPD) or 94% in all other patients. Cardiovascular sedation-related side-effects include heart rate or blood pressure reduction greater than 20% from baseline, but such events may be related to spinal anaesthesia rather than the sedation. All such events will be noted by a study investigator and reviewed to determine the likely aetiology. There are no objective clinical criteria to determine this, but routine clinical practice is to assimilate the presented information to estimate the likely contribution from sedation, spinal anaesthesia and/or another cause.To determine whether patients undergoing PMPS experience different health-related quality of life outcomes compared to patients undergoing ACPS.

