
### Study design and setting

The trial is an open-label, randomised, controlled superiority trial recruiting adults who are undergoing elective primary lower-limb arthroplasty with sedation by propofol infusion by effect-site targeting into two equal-sized parallel arms: PMPS and ACPS. The study will be run as a single-centre study at Nottingham University Hospitals National Health Service (NHS) Trust. The trial will be conducted only in a secondary care setting.

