### Sample size calculation

Our calculation is based on results from a pilot PMPS study (*n* = 26) and prospectively gathered standard care ACPS (*n* = 17), showing that the mean body-weight-normalised rate of propofol consumption in the PMPS and ACPS groups was 1.580 (SD = 0.755) and 2.231 (SD = 0.915), respectively. For power of 90% and level of significance of 5% against the two-sided alternative hypothesis, 72 participants are required to detect the observed difference in mean rate using Welch’s two-sample *t* test. Expecting 10% drop-out of participants, a sample size of 80 is required. Participants who drop out from the trial prior to randomisation will be removed from the study and any trial data that may have been collected on them or from them will be destroyed. All participants dropping out after randomisation will be included in the study by intention to treat and all trial data collected up to the moment of drop out will be retained for analysis.

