### Statistical plan

All data collected will be summarised for reporting purposes using descriptive statistics. The hypothesis test associated with the primary outcome will compare the two mean consumption rates using standard statistical tests chosen appropriate to underlying assumptions (e.g. two-sample *t* test and the Wilcoxon-Mann-Whitney test). Testing will be performed using datasets formed according to inclusions based on intention to treat. *P* values will be reported, with values less than 5% declared statistically significant.

We will report analyses of secondary outcomes for complete cases that contain no major clinical investigation plan violations. Amongst these, button-press data will be modelled using count data regression methods, with extension to bivariate models to distinguish between successful presses and unsuccessful presses. The panel time-series of propofol consumption rates collected throughout the sedation period alongside button presses will together be modelled using marked-point process methods. Ordinal responses recorded on a Likert scale (peri-operative anxiety, patient satisfaction) will be compared across trial arms using parametric methods suitable to underlying assumptions and non-parametric methods, such as the Wilcoxon rank sum test. Preoperative and post-operative quality of recovery total scores will be compared using the Wilcoxon matched pairs test. Inter-item correlations will be computed and associations between scored items will be compared using Spearman rank correlation. The Bonferroni correction to allow for multiple comparisons will be applied. Qualitative data obtained from structured questions will be coded and computer-analysed. Any missing outcome data will be imputed using either a last-observation-carried-forward rule or, for the subset of comparable secondary outcomes, use data routinely measured and recorded as part of usual clinical care.

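### The only test named for the quality of recovery score compares time points within patients, so it gives no PMPS versus ACPS comparison for that outcome

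*Protocol article*

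**What the plan says.** The Statistical plan section of the protocol article gives quality of recovery one sentence: "Preoperative and post-operative quality of recovery total scores will be compared using the Wilcoxon matched pairs test". The two things compared are the two time points. The arms are not mentioned, and the text does not say whether the test is pooled over all patients or run within each arm.

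The sentence just before it treats other outcomes differently. Peri-operative anxiety and patient satisfaction "will be compared across trial arms using parametric methods suitable to underlying assumptions and non-parametric methods, such as the Wilcoxon rank sum test".

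The trial randomises patients "into two equal-sized parallel arms: PMPS and ACPS" (Study design and setting), and the Background states its purpose: "Our aim is to assess the clinical efficacy of PMPS compared to ACPS". Quality of recovery is not named in the Study objectives. The nearest listed objective concerns health-related quality of life and is worded as a contrast between arms: "To determine whether patients undergoing PMPS experience different health-related quality of life outcomes compared to patients undergoing ACPS". EQ-5D-5L is mentioned only in the health economic paragraph.

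**The concern.** A matched-pairs test works on each patient's post-operative minus pre-operative difference and asks whether those differences centre on zero. That is a question about the peri-operative course, not about the randomised treatment. In a two-arm parallel trial, a plan that names only this test for an outcome fixes the wrong contrast for it.

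Two things are at stake. If the test is pooled, a clear result shows only that patients in general recover or deteriorate, and a real arm difference can go unseen. If it is run per arm, the output is two p-values, and a report can easily read significance in one arm and not the other as a treatment effect. That reading is not a test of the arm difference.

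**Working it through.** **1. Side by side.** Both sentences are in the Statistical plan section.

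| Outcome | What is compared | Named test |
|---|---|---|
| Anxiety, satisfaction | PMPS v ACPS | parametric, and non-parametric such as rank sum |
| Quality of recovery | before v after surgery | matched pairs |

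The article states the between-arm contrast for the first row and a different contrast for the second. It has not left the method open.

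**2. The plan's own figure.** There is none for quality of recovery. The illustration below takes 36 per arm from the primary sample size, so that figure is checked first. Inputs (Sample size calculation): the mean rates for PMPS and ACPS "was 1.580 (SD = 0.755) and 2.231 (SD = 0.915), respectively", and "For power of 90% and level of significance of 5% against the two-sided alternative hypothesis, 72 participants are required".

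- Difference: 2.231 − 1.580 = 0.651, and 0.651 / 2.231 = 29.2%.
- Welch power from the noncentral t distribution: 0.892 with 35 per arm (total 70) and 0.901 with 36 per arm (total 72). The stated 72 reproduces.
- Dropout: 72 / 0.9 = 80. The stated 80 reproduces.

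**3. Per-arm reading, no true arm difference.** Assumptions, none of them from the document: 36 pairs per arm, two-sided 5% in each arm, paired-t approximation to the matched-pairs test, and the same true change d in both arms, in SDs of the paired differences. The noncentrality is d × √36 = 6d, with critical value 2.030 on 35 df. If each arm is significant with probability p, the two arms disagree with probability 2p(1 − p).

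| d | p | 2p(1 − p) |
|---|---|---|
| 0 | 0.050 | 9.5% |
| 0.3 | 0.417 | 48.6% |
| 0.4 | 0.646 | 45.8% |
| 0.5 | 0.831 | 28.1% |
| 0.6 | 0.938 | 11.6% |
| 0.7 | 0.983 | 3.3% |
| 0.8 | 0.997 | 0.7% |

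The right comparator is the 9.5% at d = 0, because two independent 5% tests disagree that often when nothing changes at all. Disagreement peaks at 50% when p = 0.5 and falls towards zero once the common change is large.

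**4. Simulation with the signed-rank test itself.** Assumptions: 36 per arm, normal scores with SD 1, pre/post correlation 0.5, 4,000 runs. The SD of the differences is then √(2 × (1 − 0.5)) = 1, so the scale matches step 3.

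| True change (PMPS, ACPS) | Pooled matched pairs significant | Per-arm tests disagree | Rank sum on change significant |
|---|---|---|---|
| −0.4, −0.4 | 90% | 46% | 5% |
| −0.5, −0.5 | 99% | 30% | 5% |
| −1.0, −1.0 | 100% | under 0.1% | 5% |
| +0.4, −0.4 | 3% | 47% | 91% |

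In the first three rows the arms do not differ. The pooled matched-pairs test is nearly always significant, while the rank-sum test on change keeps its 5%. In the last row the arms differ by 0.8 SD. The pooled test rejects in 3% of trials and the between-arm test in 91%.

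**The case against.** The strongest reply is that the document gives quality of recovery no objective, so a before/after test may be meant only to describe recovery and is legitimate for that. It stands that no listed objective names this score, and that the link runs through the general aim and, more loosely, the quality-of-life objective. But no listed objective asks whether scores change from before to after surgery either, and this is the only test named for the outcome. An analysis plan that is not shown might add an arm comparison, but the published sentence would still state the wrong contrast.

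Three stronger readings are tempting, and the document does not support them.

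- *The anxiety and quality-of-life objectives also go unanswered.* The anxiety objective ("To assess whether patients undergoing PMPS have equal reductions in peri-operative anxiety compared to patients undergoing ACPS") is served by the across-arm comparison in the preceding sentence. The matched-pairs test is not assigned to EQ-5D-5L, whose before/after data feed an economic comparison of PMPS with ACPS.
- *The plan wrongly leaves out baseline adjustment.* A condensed article commonly leaves covariates to the full plan, so its silence is no fault. Adjustment appears below only as one way to make the comparison.
- *The plan carries a false-difference rate of 28% to 49% against a nominal 5%.* Those figures belong to d between 0.3 and 0.5 and to a per-arm reading followed by a comparison of p-values, neither of which the text states. They fall below 1% at d = 0.8, and the no-change comparator is 9.5%. They also use an unadjusted 5% level, although the plan mentions a Bonferroni correction, and 36 pairs per arm, although secondary outcomes are analysed in complete cases without major violations.

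**Conclusion.** The point holds for quality of recovery alone. As written, the plan yields neither a test nor an estimate of the PMPS versus ACPS difference on this score, under either the pooled or the per-arm reading. That conclusion follows from what the statistic uses and needs no assumption about effect size. The simulated and calculated rates, including the range of about 1% to 49%, only illustrate it and depend on the assumptions listed with them.

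This is a secondary outcome, and the primary comparison and the sample size of 72, raised to 80, stand. It is worth correcting because the wording is definite and the remedy is cheap.

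**What to change.** Replace the sentence with a between-arm comparison of the quality of recovery total score. Either of these would do:

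- the post-operative score compared between PMPS and ACPS, adjusted for the same patient's pre-operative score (ANCOVA or an ordinal equivalent); or
- a rank-sum test of post-operative minus pre-operative change between arms.

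Report the arm difference with a 95% CI. The matched-pairs result may stay as a description of change within each arm, with a statement that the two within-arm p-values are not to be compared.

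The cost is one sentence of analysis wording. Both scores are already to be collected, so no new data, visits or participants are needed. The Statistical plan section already commits to describing and justifying departures from the plan, so the change can be recorded there.

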**Discussion:**

This is the first trial to test the superiority of effect-site-targeted patient-maintained propofol sedation versus anaesthetist-controlled propofol sedation in terms of total propofol consumption during the sedation period. The results of this trial will help inform clinicians and device manufacturers of the clinical efficacy and safety of patient-maintained propofol sedation applied to a common operative setting.

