### Statistical methods

Propofol consumption (milligrams) will be calculated in participants randomised to the two study groups. Body weight (kilograms) and height (centimetres) recorded at the pre-operative assessment will be used. Length of sedation is defined as the time from when the propofol sedation is commenced by the supervising clinical anaesthetist up until the time when the first skin clip is inserted to close the wound (at which point the anaesthetist will stop the sedation).

The alternative hypothesis is two-sided. The level of statistical significance is 5%. The clinical superiority of PMPS over ACPS will be shown if the mean rate is reduced by 29% (or more) when using PMPS, compared with ACPS. The randomisation schedule will be computer-generated using an 8-block design, with allocation advised by opaque sealed envelope. The expected recruitment rate into the study is 2 patients per week.

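### The Bonferroni correction is stated without a family and without exempting harms; if it covers the side-effect comparison, it lowers the chance of detecting excess harm with the prototype device

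*Protocol article*

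**What the plan says.** All references are to the protocol article.

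- **Study objectives.** The seventh of eight secondary objectives is "To determine whether patients undergoing PMPS experience a different incidence of airway, respiratory or cardiovascular sedation-related side-effects than patients who have undergone ACPS". It covers three classes of event. No expected rate is given for any of them.
- **Statistical plan, second paragraph.** This paragraph deals with secondary outcomes, analysed in complete cases without major violations. It goes through button presses, consumption over time, anxiety and satisfaction scales, quality-of-recovery scores and inter-item correlations. It then states "The Bonferroni correction to allow for multiple comparisons will be applied". The family and the number of comparisons are not given, harms are not exempted, and no test for side-effects is named.
- **Abstract, Discussion.** "The results of this trial will help inform clinicians and device manufacturers of the clinical efficacy and safety of patient-maintained propofol sedation". The abstract's background also names collecting safety data on the prototype device as a purpose of the trial.
- **Statistical methods and Sample size calculation.** The only sizing is for propofol consumption: "For power of 90% and level of significance of 5% against the two-sided alternative hypothesis, 72 participants are required", and then "Expecting 10% drop-out of participants, a sample size of 80 is required".

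**The concern.** Bonferroni limits false positive findings in either direction, at the cost of more missed differences. For secondary efficacy and patient-reported outcomes that trade is usually acceptable. For harms of a prototype device the more costly error is the missed signal. If side-effects share a family with anxiety, satisfaction, discharge readiness and quality of life, the evidence needed to flag an excess of airway or respiratory events rises with the number of unrelated outcomes counted.

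The scope is better settled before data are seen. The Statistical plan says that deviations from it will be described and justified, so taking harms out of the correction afterwards could look like a choice driven by results.

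**Working it through.** **1. The plan's own sample size.** Inputs, in mg/kg/h for PMPS then ACPS: "1.580 (SD = 0.755) and 2.231 (SD = 0.915), respectively". The difference is 2.231 − 1.580 = 0.651. With 36 per arm, SE = √[(0.755² + 0.915²)/36] = √(1.40725/36) = 0.1977, so the noncentrality is 0.651/0.1977 = 3.29 on about 67.6 Satterthwaite degrees of freedom. Welch power is 90.1% at 36 per arm and 89.2% at 35. Hence 72 in total, and 72/0.9 = 80. Both stated figures reproduce. They imply at most 40 per arm for any side-effect comparison.

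**2. Inputs for the side-effect check.**
- From the article: 40 per arm (80 in two equal arms), two-sided, 5% significance level.
- Assumed: the event rates, the test, and the number of comparisons k. I take k = 1 (no correction), k = 3 (the three side-effect classes) and k = 8 (the listed secondary objectives). The thresholds are 0.05, 0.05/3 = 0.0167 and 0.05/8 = 0.00625.

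**3. Method.** For counts x₁ and x₂ out of n, z = [(x₂ − x₁)/n] / √[2p̄(1 − p̄)/n], where p̄ = (x₁ + x₂)/(2n). The miss rate is the total binomial probability of all pairs (x₁, x₂) whose two-sided p exceeds the threshold.

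Hand check for 10% against 30%: the null SE is √(2 × 0.2 × 0.8/40) = 0.0894 and the alternative SE is √[(0.1 × 0.9 + 0.3 × 0.7)/40] = 0.0866. Power ≈ Φ[(0.20 − z_crit × 0.0894)/0.0866]. With z_crit = 1.960, 2.394 and 2.734 this gives 61%, 44% and 30%, that is, miss rates of 39%, 56% and 70%. The exact results below agree closely.

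**4. Miss rates for a tripling, 40 per arm (exact enumeration, chi-squared).**

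| Rates | k = 1 | k = 3 | k = 8 |
|---|---|---|---|
| 5% to 15% | 65% | 84% | 93% |
| 10% to 30% | 37% | 56% | 71% |
| 13% to 39% | 22% | 38% | 53% |
| 15% to 45% | 15% | 28% | 41% |
| 20% to 60% | 3% | 8% | 15% |

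By Fisher's exact test, 10% against 30% is missed 47%, 66% and 79% of the time. A tripling is missed more often than not for base rates up to roughly 13% with k = 8, and up to about 11% with k = 3.

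**5. Fewer patients.** Secondary analyses use complete cases without major violations, so 40 per arm is an upper limit. At 36 per arm, the 10% against 30% miss rates are 42%, 61% and 74%.

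**6. How much is due to sample size.** From 5% to 15%, the test already misses about two times in three with no correction. By the normal approximation, 80% power would need 141 per arm at 0.05 and 229 at 0.05/8.

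**7. What one result would look like.** The counts expected at 10% and 30% are 4/40 and 12/40. Then z = 0.20/0.0894 = 2.24, p = 0.025: below 0.05, above 0.0167 and 0.00625. The risk difference is 20 points with a Wald 95% interval of 20 ± 1.96 × 8.66, about 3 to 37 points. With 4/40 in both arms the difference is 0, but the interval is 0 ± 1.96 × 6.71, about −13 to +13 points. The interval conveys what a bare test result would hide in either case.

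**The case against.** **The sentence may not reach the harms.** It directly follows the Spearman correlations between scored items, a natural place for a correction, and the paragraph never mentions side-effects. This stands as a possible reading. But the wording is unqualified, the paragraph is about secondary outcomes, and side-effect incidence is one of them. A rule that can be read both ways on this point needs one more clause.

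**The details may be in a fuller plan.** The family, the safety test and the intervals are often left there, and their absence from an article is no fault. The point here is narrower: the article does fix a rule, and as worded the rule takes in harms.

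**Safety does not hang on one test.** A reader might infer that even a tripling of harm would mostly be reported as no difference. The documents do not support that. Nowhere do they say that a non-significant result will be so reported. All data are to be summarised descriptively, side-effects are reviewed for likely cause, and adverse events and adverse device events are recorded and reported whatever any p value shows. The sentence declaring significance below 5% closes the paragraph on the primary test.

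**The size depends on assumptions.** This is right. From a 15% or 20% base, a tripling is missed only 41% or 15% of the time with k = 8. Cardiovascular events, which the article says may come from the spinal, could be common, and a rate above one third cannot triple. For rare events, dropping the correction leaves most of the problem in place.

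**Conclusion.** The point holds in conditional form. The article states a Bonferroni correction without its family and without exempting harms, and a plain reading includes the between-arm side-effect comparison. If it is included, the correction materially lowers the chance of detecting excess harm: for 10% against 30% at 40 per arm, the miss rate rises from 37% to 56% with three comparisons or 71% with eight. Event rates, number of comparisons and choice of test are assumptions. It would be wrong to conclude that the correction certainly applies to harms, that large excesses would generally be missed whatever the base rate, or that the correction is the main obstacle for rare events. This is an inexpensive improvement to the analysis wording; it does not touch the primary analysis.

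**What to change.** In the Statistical plan:

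- Confine the Bonferroni correction to the secondary efficacy and patient-reported comparisons, and say that side-effects lie outside it.
- For each of the airway, respiratory and cardiovascular classes, report counts by arm and the unadjusted risk difference (PMPS minus ACPS) with a 95% confidence interval.
- State that a non-significant difference will not be read as equal safety, and that any safety statement will refer to the upper limit of the interval.

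This is a change of wording only, with no new data, no change in sample size and no effect on the primary test. The downside is somewhat more chance flags among the harms, which the intervals and the planned review of each event help put in context. It does not cure the low power for rare events; it makes the remaining uncertainty visible.

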### Post-operative period

Participants will be transferred to the PACU where a study investigator will continue physiological and sedation outcome measures until readiness for discharge from PACU is achieved. The modified Aldrete score will be recorded at 5-min intervals from the time the sedation regime stops until the time at which the participant is scored in excess of 9, indicating readiness for safe discharge from PACU. Once participants are ready for discharge from PACU a study investigator will administer a short, group-specific post-operative questionnaire including questions on psychological variables (e.g. anxiety).

On post-operative day 7–10 (the exact timing depending on the availability and convenience of the participant), a study investigator will contact all patients by telephone to conduct a group-specific post-operative telephone questionnaire (including questions on anxiety since the operation and the sedation experience) and a brief structured interview (in order for us to gain more in-depth data on the experience and perceptions of the sedation experience for patients in the PMPS group). The interview will include qualitative responses in order to allow the participant to provide additional information beyond that covered in the questionnaires.

On completion of the post-operative telephone questionnaire the participant’s enrolment in the trial will cease. A SPIRIT schedule of trial enrolment, intervention and assessment is shown in Fig. 1.

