Health economic analysis aims to establish the net monetary benefit due to the NHS from introducing PMPS compared to the current practice of ACPS. Economic modelling will rely on parameterisations developed from the data gathered from all trial outcome measures, including health-related quality of life from the Euroqol (EQ)-5D-5 L questionnaire before/after data. These data will be collected as part of the pre-operative and post-operative participant interviews. Cost differentials across the two trial arms are expected due to propofol use and time to fitness for discharge from PACU.

No interim analyses are planned for this study. Any deviation from the original statistical plan will be described and justified in the final report.

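### Two conflicting missing-data rules for secondary outcomes, one of which (last observation carried forward) records zero change for before/after scores

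*Protocol article*

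**What the plan says.** Three statements on who is analysed and what is filled in stand close together in the Statistical plan section of the protocol article:

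- For the primary outcome: "Testing will be performed using datasets formed according to inclusions based on intention to treat".
- For secondary outcomes: "We will report analyses of secondary outcomes for complete cases that contain no major clinical investigation plan violations".
- At the end of the paragraph on secondary outcomes: "Any missing outcome data will be imputed using either a last-observation-carried-forward rule" or, as the alternative, "for the subset of comparable secondary outcomes, use data routinely measured and recorded as part of usual clinical care".

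The outcomes that these rules must serve differ in shape:

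- **Quality of recovery** is a before/after pair: "Preoperative and post-operative quality of recovery total scores will be compared using the Wilcoxon matched pairs test".
- **EQ-5D-5L** is also a pair. The health economic paragraph relies on "health-related quality of life from the Euroqol (EQ)-5D-5 L questionnaire before/after data".
- **Anxiety** is judged by its reduction (Study objectives). The Post-operative period section places anxiety questions in the PACU questionnaire and again at day 7-10, when "a study investigator will contact all patients by telephone to conduct a group-specific post-operative telephone questionnaire".
- **Physiology, depth of sedation and the Aldrete score** are recorded every 5 minutes (Safety, Intervention and Post-operative period sections).

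The Sample size calculation section adds that participants who drop out after randomisation stay in by intention to treat, with their data up to that point.

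**The concern.** A complete-case analysis contains no missing values by construction, so a rule that imputes any missing outcome cannot operate inside it. The imputation sentence names secondary outcomes in its second limb, so it cannot be read as meant for the primary outcome alone. Nothing says which rule prevails, or which outcomes take the carried-forward value and which take routine records. Each secondary outcome could therefore be analysed in two ways, and in an open-label trial the choice could be made after the data are seen.

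The second issue is the imputation rule itself. For an outcome with one value before surgery and one after, the last observation before a missing post-operative score is the pre-operative score. Carrying it forward asserts that surgery and sedation changed nothing for that person. That pulls both arms' changes towards zero and so towards each other, which suits an objective framed as equal reductions in anxiety. For EQ-5D-5L the forced zero also enters the economic model. The filled-in values are then counted as if they had been observed.

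**Working it through.** **The plan's own figure.** The only checkable figure near this point is the sample size, and it reproduces. The pilot means differ by 2.231 - 1.580 = 0.651, with SDs 0.755 and 0.915. For a two-sided 5% Welch test, power is 0.8923 at 35 per arm and 0.9007 at 36 per arm, so 72 are needed. Then 72 / 0.90 = 80. The concern does not touch this figure.

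**Where carrying forward reaches back to the pre-operative value**

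- Quality of recovery and EQ-5D-5L: yes, if the post-operative score is missing. This assumes that Fig. 1 lists no further post-operative administration.
- Anxiety with neither a PACU nor a telephone score: yes.
- Anxiety missed only at day 7-10: no. The PACU score is carried.
- 5-minute series: no, for a gap within the series. The value carried is the preceding recording.
- Satisfaction: no. There is no pre-operative value to carry.

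**Shrinkage.** Let p be the share with the post-operative value missing, unrelated to the outcome, and let μ be the true mean change. Each imputed change is 0, so

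expected change after imputation = (1 - p) × μ + p × 0 = (1 - p) × μ.

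With the same p in both arms, the arm difference in change becomes (1 - p) × (true difference).

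- p = 0.10: 90% of the true change and of the true difference remains.
- p = 0.20: 80% remains.

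Neither share is a documented rate of missing questionnaires. The 10% borrows the drop-out allowance from the sample size.

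**Unequal loss (illustrative assumption).** Suppose 15% is missing in PMPS and 5% in ACPS, with the same true change of 1 SD (SD of the change) in both arms. The expected changes are 0.85 SD and 0.95 SD, a spurious difference of 0.10 SD. The standard error of a difference is √(2/36) = 0.236 SD at 36 per arm, or √(2/40) = 0.224 SD at 40 per arm. The artefact is therefore 0.10 / 0.236 = 0.42 to 0.10 / 0.224 = 0.45 of a standard error.

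The direction is not fixed once loss is unequal. With true changes of -2 (PMPS) and -1 (ACPS), a true difference of -1:

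- 15% v 5% missing: -2 × 0.85 + 1 × 0.95 = -0.75.
- 5% v 15% missing: -2 × 0.95 + 1 × 0.85 = -1.05.

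**Precision.** With 40 per arm and σ the SD of the change, the variance of the partly imputed change is (1 - p)σ² + p(1 - p)μ². At p = 0.10 and σ = 1:

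- μ = 0: √(0.90 / 40) = 0.150 SD.
- μ = 1 SD: √(0.99 / 40) = 0.157 SD.
- From the 36 observed values alone: √(1 / 36) = 0.167 SD.

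The imputed analysis reports a smaller standard error around a shrunken estimate.

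**A limit.** These formulas concern means. The usual form of the Wilcoxon matched pairs test discards zero differences, so imputed pairs would add nothing to that p value for quality of recovery. The reported mean changes, and any comparison of changes between arms that retains the imputed zeros, would still be affected.

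**The case against.** The strongest reply has four parts.

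**The two complaints are alternatives.** If the complete-case sentence governs, carrying forward never reaches the secondary outcomes and the shrinkage does not arise. This stands: the bias is conditional on one reading. A partial reconciliation is also possible, in which gaps within the records of otherwise complete participants are filled. The article does not say so, and the need to state one rule remains.

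**Carrying forward is often milder than it sounds.** A gap in a 5-minute series takes a recent value, and a missed telephone call takes the PACU anxiety score. Routine clinical records are a stated alternative and could supply real values for charted measures, plausibly including recovery observations. This also stands. A reader might infer that every before/after change is distorted, or that a participant with a missing Aldrete score is never counted as ready for discharge. The documents do not support either as a general statement.

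**The primary outcome.** A reader might infer that the primary comparison is biased, because the rule covers any missing outcome. The documents do not show this. Consumption rates are collected as a series throughout sedation, data up to drop-out are retained, and the rate can be computed from the infusion record.

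**The size is assumed and small.** The 10% is an allowance made for the primary outcome. The 15% v 5% split and the 1 SD change appear nowhere in the article, and even these give less than half a standard error on a secondary outcome. This is fair and limits the severity.

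Outcome-by-outcome detail can be left to a fuller plan, but that does not dispose of the point: the article states a rule, and it conflicts with another in the same paragraph.

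**Conclusion.** The concern holds in a limited form. The Statistical plan gives two incompatible rules for secondary outcomes. Where the only earlier value is pre-operative, carrying it forward forces zero change. If the missing share is equal in both arms and unrelated to outcome, mean change and any true arm difference in change shrink by that share: 10% at an assumed 10% missing, 20% at an assumed 20%. The effect favours a finding of equal anxiety reduction, and the standard error is too small (0.150 to 0.157 SD against 0.167 SD in the illustration). With unequal loss, a false difference can appear in either direction.

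The harm is confined to secondary and economic outcomes. The primary test and the sample size are not shown to be affected. This is a should-fix point.

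**What to change.** State one missing-data rule for the secondary outcomes and delete last observation carried forward for them. Specifically:

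- **Single post-operative scores** (quality of recovery, EQ-5D-5L, anxiety): compare arms in all randomised participants with an observed post-operative score, adjusted for the baseline score. Add multiple imputation (arm, baseline score, age, sex, hip or knee) as a sensitivity analysis.
- **5-minute repeated measures:** use likelihood-based mixed models, which use the recorded values without filling gaps.
- **Routine clinical records:** keep them as a source of real values, and name the outcomes to which they apply.
- **Primary rate:** state that it is computed from the infusion record available for each participant.

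The cost is revised wording, modest extra analysis and slightly wider intervals. Recruitment and data collection do not change. The article already allows deviations from the statistical plan if they are described and justified, and this one should be fixed before the data are analysed.
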